## Abstract

**ABSTRACT:**

**Introduction:**

Pancreatic ductal adenocarcinoma (PDAC) continues to have extremely poor patient outcomes, unlike other cancer types which have seen significant improvements in their treatments and survival. A major contributing factor is that PDAC is often detected at an advanced, incurable stage. In the UK, nearly half of patients have stage 4 disease at the time of diagnosis, which has a profound effect on treatment options and, ultimately, survival. To address the challenge of early detection of PDAC, this study aims to develop and validate a clinical prediction model based on a non-invasive breath test. The proposed breath test aims to assist general practitioners in the triaging of patients who present with symptoms that do not meet current criteria for urgent suspected PDAC pathway referral.

**Methods and analysis:**

The Volatile organic compound Assessment in Pancreatic ductal adenOcaRcinoma (VAPOR 1) study is a prospective, multicentre, case–control study that aims to recruit 771 participants from England, Wales and Scotland. These include adult participants, aged ≥18 years, in three cohorts: pancreatic ductal adenocarcinoma; benign pancreatic controls (chronic pancreatitis or new-onset diabetes); healthy controls with a normal pancreas on imaging. A one-off breath sample will be obtained from participants who have fasted for at least 6 hours, and participant demographics and clinical data will be recorded. Breath samples will be analysed using gas chromatography–mass spectrometry to identify the volatile organic compounds (VOCs) present. Relationships between VOCs of interest and the presence of PDAC will be explored, and a clinical prediction model will be developed using statistical and machine learning methods and internally validated.

**Ethics and dissemination:**

The VAPOR 1 study has received approval from the South East Scotland Research Ethics Committee 02, and from the Health Research Authority and Health and Care Research Wales (REC 22/SS/0061). Results of this study will be published in open-access peer-reviewed journals, and disseminated through pancreatic cancer conference presentations. In addition, lay summaries shared on our website, social media platforms and through our charitable funder, Pancreatic Cancer UK, will enable engagement with patients and the wider public.

**Trial registration number:**

NCT05727020.

STRENGTHS AND LIMITATIONS OF THIS STUDYThe study includes a benign cohort with new-onset diabetes to minimise potential confounding caused by the presence of diabetes in some patients diagnosed with pancreatic cancer.Volatile organic compound (VOC) analysis from breath samples follows a standardised process using validated gas chromatography–mass spectrometry methods.The study design is aligned with similar clinical studies investigating different gastrointestinal cancer types to facilitate the development of an integrated prediction model for early detection of multiple gastrointestinal cancers.Participant recruitment occurs in secondary care environments, while the ultimate test is intended for use in primary care.Participants receiving antibiotics within 8 weeks are excluded from the study, which could impact the application of the diagnostic prediction model in the clinical setting.

## Introduction

### Diagnostic challenges of pancreatic ductal adenocarcinoma

 Pancreatic ductal adenocarcinoma (PDAC) is the fifth most common cause of cancer-related deaths worldwide,^1^ and the incidence is expected to rise. Between 2006 and 2016, the number of deaths due to PDAC increased by 30%.^2^ In the UK, PDAC is the 10th most common type of cancer, but due to the challenges faced with early diagnosis and a lack of effective treatments for advanced disease, survival remains extremely poor. This makes it the fifth most common cause of cancer-related mortality in the UK (based on 2017–2019 data).^3^ PDAC is expected to become the second most common cause of cancer-related mortality in the USA by 2030.^4^

Pancreatic cancer does not usually cause symptoms in the early stages. The most common initial symptoms of PDAC are indigestion, loss of appetite, fatigue and ‘feeling different’, all of which are also common in patients without cancer.^5^ This makes early diagnosis of pancreatic cancer a significant challenge, as demonstrated by the longer time interval between first presentation in primary care and diagnosis, compared with other cancers.^6^ As a result, PDAC is frequently diagnosed at an advanced stage, when curative treatment options are limited.

The outlook for PDAC patients has improved only minimally over the last 50 years, with currently only 5% of those diagnosed surviving beyond 10 years, compared with 1% in the 1970s.^3^ The failure to improve survival of PDAC is largely a consequence of failure in the diagnostic pathway; therefore, early detection of PDAC remains an unmet clinical need.^7^

There is currently no screening programme available for pancreatic cancer in the UK general population, although the European Registry of Familial Pancreatic Cancer and Hereditary Pancreatitis trial screens high-risk genetically susceptible individuals.^8^ Thus, existing pathways for PDAC detection are based on referrals for patients either with symptoms or incidental findings of PDAC during investigations being undertaken for other reasons. These pathways currently use cross-sectional imaging (eg, CT, MRI) or endoscopic ultrasound to diagnose suspected PDAC, with pancreatic biopsy and histological confirmation for definitive diagnosis. The invasive nature of the gold standard diagnostic investigations, in addition to the non-specific symptoms associated with PDAC, underlies the challenges in diagnosis. For patients with non-specific symptoms, these invasive procedures and exposure to ionising radiation will frequently lead to over-investigation, as most patients will have benign pathology. In addition, patients are subject to unnecessary anxiety, and there are cost consequences to healthcare systems. In contrast, an overly cautious approach to referring patients with non-specific symptoms may result in missed or delayed cancer diagnoses. Therefore, alternative, more acceptable methods are required to help improve early detection of PDAC and reduce unnecessary testing.

### Proposed solution

A triage test will overcome the challenge of earlier detection of PDAC, by better targeting patients for referral to the appropriate specialised tests. Breath testing has ideal characteristics for a triage test. It is non-invasive, simple to undertake, relatively cheap, safe and universally acceptable to patients of all ethnicities.^9^ Such a test would directly benefit patients presenting with non-specific symptoms who do not meet existing criteria for referral. The proposed test is based on the detection of volatile organic compounds (VOCs), which are carbon-containing compounds that are sufficiently volatile to be detectable in the gas phase at room temperature and can be found in exhaled breath. Pilot studies in a range of cancers of the digestive system, including PDAC, have suggested that a VOC-based exhaled breath test may be sensitive and specific enough to identify patients at risk of PDAC, when used as a triage test.^10^

### Objectives

The objective of the VAPOR 1 (Volatile organic compound Assessment in Pancreatic ductal adenOcaRcinoma) study is to develop and internally validate a clinical prediction model (CPM) to triage the risk of PDAC based on profiles of VOCs obtained from the non-invasive breath test. The clinical utility of the model to enable referral for the appropriate reference test will be investigated, and the additional value of patient and clinical characteristics will be assessed. This will then be compared against the current standard practice for all patients presenting with symptoms indicative of pancreatic cancer.

## Methods and analyses

### Study design

VAPOR 1 is a UK prospective case–control study to construct a PDAC detection model based on VOCs in exhaled breath. The study involves the collection of breath at a single time point from eligible participants and is open to all National Health Service (NHS) trusts and diabetes education centres within the UK. The VAPOR 1 study is sponsored by Imperial College London and has obtained NIHR Clinical Research Network portfolio adoption to support study recruitment.

### Study duration

The VAPOR 1 study commenced in December 2022 and is due to be completed by August 2025.

### Definitions of study groups

VAPOR 1 has a case–control study design, with three groups of participants: PDAC, benign conditions and healthy controls.

PDAC: participants who either have a confirmed diagnosis of PDAC according to a biopsy or tissue sample taken from the pancreas, or who are due to undergo surgical resection for suspected PDAC (with histological confirmation to follow within 3 months).

Benign pancreatic conditions: participants with either new-onset diabetes mellitus (diagnosed within the previous 6 months) or chronic pancreatitis diagnosed clinically or radiologically at any time. Diabetes mellitus is confirmed if the participant’s average circulating blood sugar level, determined by glycated haemoglobin, is greater than 48 mmol/mol at the time of diagnosis.

Negative control group: participants with a radiologically normal pancreas confirmed by abdominal imaging, ideally within the previous 12 months.

### Eligibility

Patients aged ≥18 years will be eligible for VAPOR 1 if they satisfy one of the three group definitions earlier.

Exclusion criteria are: previous treatment (surgery, chemotherapy or radiotherapy) for confirmed PDAC; active infection, antibiotics or immunosuppressive medication within the preceding 8 weeks; any cancer in the previous 5 years; surgery altering the anatomy of the upper gastrointestinal tract (eg, Roux-en-Y gastric bypass, Whipple’s procedure); pregnancy; unable to provide a breath sample; unable to provide written informed consent.

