#### Derivation of diagnostic rules

A clinical decision rule will be derived from probabilities of PDAC generated by the final CPM, with thresholds for referral for definitive testing, review within 6 months and discharge.

Development of decision rules will consider the cost of missing a PDAC case and of incorrectly declaring PDAC in the control group. The net benefit of the CPM will be calculated across a range of candidate thresholds.^17^ We will use decision curve analysis^18^ to compare the net benefit of the proposed CPM against the current standard of care of referring all symptomatic patients. We will also consider the threshold which maximises the expected number of patients taking the test before misdiagnosis occurs, weighted by the ‘clinical cost’ of a false negative relative to a false positive.^19^ This relative ‘clinical cost’ will be elicited from expert clinicians and members of the study steering group, which includes patient representatives.

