#### Data collection and management considerations

Prior to providing a breath sample, eligibility criteria will be assessed and recorded by the research team member, including dates and results of eligibility tests. Participant demographics and baseline lifestyle factors, medications, medical history, family history of cancer and symptoms will be recorded in the VAPOR REDCap database. This is a secure online database with access limited to the research staff trained on study procedures and authorised on the study delegation log. Data monitoring will be conducted through both central monitoring of the REDCap database and on-site monitoring visits to conduct source data verification. Breath samples will be processed according to our standardised laboratory workflow which ensures full traceability of participants’ breath samples by logging recorded data on our Laboratory Information Management System. Participants’ VOC profiles will be obtained via mass spectrometry during breath sample analysis, and this will be recorded alongside their clinical data (see online supplemental table 1 which lists the data collected). Where a participant withdraws consent, this will be recorded on the REDCap database. All data and samples collected up to the point consent was withdrawn will be kept for analysis. No further breath samples will be obtained; however, data related to existing samples may still be collected.

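### The decision curve compares the model with referring all symptomatic patients, but no control has to be symptomatic, so net benefit can rest partly on people outside that comparison

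*Protocol article*

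**What the plan says.** The Abstract (Introduction) gives the test's purpose as the "triaging of patients who present with symptoms that do not meet current criteria for urgent suspected PDAC pathway referral". The Objectives carry this into the evaluation: "This will then be compared against the current standard practice for all patients presenting with symptoms indicative of pancreatic cancer". The section Derivation of diagnostic rules makes it operational through decision curve analysis, to "compare the net benefit of the proposed CPM against the current standard of care of referring all symptomatic patients". The same section weighs the cost of a missed cancer against the cost of wrongly calling PDAC among the controls.

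Entry is wider. Under Eligibility, "Patients aged ≥18 years will be eligible for VAPOR 1 if they satisfy one of the three group definitions earlier". The benign group is "participants with either new-onset diabetes mellitus (diagnosed within the previous 6 months) or chronic pancreatitis diagnosed clinically or radiologically at any time", and the negative controls are "participants with a radiologically normal pancreas confirmed by abdominal imaging, ideally within the previous 12 months". Neither definition mentions symptoms. Under Participant recruitment, controls come from hospital lists, diabetes services and general-practice referrals, and symptoms are not a selection criterion.

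Symptoms are collected: "medical history, family history of cancer and symptoms will be recorded in the VAPOR REDCap database". The model-development section names presenting symptoms as possible additional predictors. No analysis restricted or standardised to symptomatic participants is stated. The limitations box mentions recruitment in secondary care for a primary-care test, but not symptom status.

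**The concern.** The clinical question is whether breath separates PDAC from other causes of the same non-specific symptoms. Net benefit against refer-all depends on the false-positive rate among people who would be referred under that strategy. As written, that rate is measured in controls who need not belong to that population. A symptom-free control whom the model calls negative counts as a referral avoided, although refer-all-symptomatic would not have referred that person.

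The thresholds for referral, later review and discharge are to be derived from the same data. An optimistic false-positive rate would therefore carry into the decision rule as well as into the reported curve. Adjusting to a target prevalence does not help: it changes the weight given to the false-positive rate, not the people in whom it is measured. Using symptoms as predictors could make matters worse, because symptom-free controls would then be separated from cases partly by the way they were recruited.

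**Working it through.** **1. The plan's own numbers.** Inputs from Sample size: sensitivity 0.85, precision 0.07, power 80%. Two-sided alpha of 0.05 is assumed, as none is stated.
- n = (1.960 + 0.842)² × 0.85 × 0.15 / 0.07² = 204.2, so 205 cases, as stated.
- With 205 of each of two control types there are 410 controls and 615 participants in total.
- 205 / 0.80 = 256.25, rounded up to 257, and 3 × 257 = 771.

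These figures reproduce and are not in dispute. What matters here is that all 410 planned controls enter without a symptom requirement.

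**2. When bias arises.** Let w be the share of controls without symptoms.
- Pooled specificity = w × Sp(symptom-free) + (1 − w) × Sp(symptomatic).
- If the two specificities are equal, the pooled value is correct whatever w is, and there is no bias.
- If symptom-free controls are easier to classify, the pooled value is too high.

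The protocol gives neither w nor either specificity.

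**3. Illustration from the planned AUC.** Assumptions: binormal scores with equal variance, and symptomatic controls scoring 0.2 or 0.3 SD above the overall control mean.
- d′ = √2 × Φ⁻¹(0.86) = 1.528.
- Specificity at 85% sensitivity = Φ(1.528 − 1.036 − shift).

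| Shift (SD) | Specificity | False-positive rate |
|---|---|---|
| 0 (all controls) | 0.688 | 0.312 |
| 0.2 | 0.615 | 0.385 |
| 0.3 | 0.576 | 0.424 |

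The false-positive rate in symptomatic controls would be 0.385/0.312 = 1.23 or 0.424/0.312 = 1.36 times the overall one.

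**4. A second illustration by mixture.** Assume specificity of 0.70 in symptomatic controls, 0.80 or 0.90 in symptom-free controls, and w of 25% to 75%. Pooled specificity then runs from 0.725 to 0.850. The symptomatic false-positive rate is 0.30/0.275 = 1.09 to 0.30/0.15 = 2.0 times the pooled one. The upper end needs both extreme assumptions together.

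**5. Net benefit.** NB = Se × prev − (1 − Sp) × (1 − prev) × t/(1 − t). Assume prevalence 1% and threshold t = 2%, so that 0.99 × 0.02/0.98 = 0.0202.
- Model, at specificity 0.688, 0.615 and 0.576: +0.0022, +0.0007 and −0.0001.
- Refer-all: 0.0100 − 0.0202 = −0.0102.
- Gain over refer-all: 0.0124, 0.0109 and 0.0101, which is 12% and 18% smaller for the two shifts.

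In this example the model still beats refer-all. The change of sign is against referring nobody.

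**6. Precision in symptomatic controls.** Half-width = 1.96 × √(0.69 × 0.31/m). If 20%, 40% or 60% of the 410 controls are symptomatic (assumed), m = 82, 164 or 246 and the half-width is 10.0, 7.1 or 5.8 points, against 4.5 with all 410.

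**The case against.** The protocol article names the method and the comparator but does not say outright who enters the decision curve, and that detail could sit in an analysis plan not shown here. Controls are largely hospital patients, many on imaging, endoscopy or clinic lists, so a good number may well have symptoms. The limitations box already concedes a related spectrum problem, and the study claims only development and internal validation. Specificity is not among the performance measures listed for cross-validation. A subset of unknown size is a fragile basis for a main analysis, and hospital-recorded symptoms are not those of the general-practice patients for whom the test is meant.

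Much of this stands and limits the claim. A reader might infer that false positives certainly come from people the test would never be offered to; the documents show only that they can. A reader might also infer that the share of controls without symptoms is the share of avoided referrals wrongly credited, and hence the error in net benefit. That does not follow: net benefit uses a rate, and if specificity is the same in both kinds of control the rate is unchanged when symptom-free controls are removed.

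The mismatch itself remains. The article does state the comparator in terms of symptomatic patients, and it does weigh false positives in the control group without qualification. The care-setting caveat does not address symptom status, and using symptoms as predictors does not define the population in which utility is judged.

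**Conclusion.** The point holds in a limited form. Following the plan as written, the false-positive side of net benefit is measured in people who need not belong to the population of the refer-all comparator. Overstated specificity is the likelier direction, but neither direction nor size can be established from the protocol. In the binormal illustration, 69% overall becomes 61% or 58% in symptomatic controls, and the gain over refer-all shrinks by 12% or 18%. These figures rest on assumed shifts, prevalence and threshold. The true effect may be nil.

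The documents do not support a stronger conclusion, such as that the comparison with refer-all would reverse or that the recruitment design is invalid. What they do support is that, without an analysis in symptomatic participants, the study cannot show that this bias is small.

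**What to change.** Leave recruitment, model development and the sensitivity target on all participants. In Derivation of diagnostic rules, pre-specify that specificity, net benefit and the decision curve are also estimated in participants, cases and controls alike, with at least one recorded presenting symptom of the kind indicative of pancreatic cancer. Fix the symptom list before analysis. Show this result beside the all-participant result, and base any conclusion against refer-all-symptomatic on it. Report the symptomatic share of each group.

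This uses data already collected. It costs precision: a half-width for specificity of about 6 to 10 points if 20–60% of controls are symptomatic, instead of 4.5. Some cases are lost too. For 85% sensitivity, 1.96 × √(0.85 × 0.15/n) is 4.9 points with 205 cases and 5.5 points with 164 (80% symptomatic, assumed). Symptoms recorded in hospital would still only approximate the primary-care target population, and the report should say so.

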### Sample size

The sample size of 205 PDAC cases was based on a target sensitivity of 85%, with 7% precision and 80% power, informed by pilot data on 132 patients.^10^ We aim to recruit the same number of each type of control, totalling 615 participants with complete data. Allowing for 20% attrition due to loss of samples, we will recruit 771 participants, which includes at least 256 with cancer.

Riley *et al*^11^ also recommend ensuring that the sample size achieves small mean absolute prediction error (MAPE), defined as the mean absolute difference between predicted and observed outcomes (cancer=1, no cancer=0), and large variation explained by the CPM, measured by Cox-Snell R^2^, which ranges from 0 for no predictive value to 1 for perfect prediction. Additionally, the area under the receiver-operating curve (AUC) provides an estimate of the ability of the CPM to discriminate between cancer and non-cancer cases. The resulting CPM based on 615 participants will have an MAPE of 0.048, estimate cancer incidence with precision 0.088, and achieve a minimum Cox-Snell R^2^ of 0.431 based on forty predictors. The SE in the AUC achieved by the CPM will be 0.016, based on an AUC of 0.86.

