A 10-fold CV will be used for internal validation of statistical and machine learning models. Nested CV will be applied to best identify the penalty terms in LASSO and elastic net models, as well as to fine-tune the hyperparameters in random forest and DNNs, reducing the risk of overfitting across all models. For each fold in the internal CV, the sensitivity, AUC, precision-recall AUC and the MAPE will be calculated and summarised by median (IQR) values across folds. Apparent performance with 95% CIs and optimism will be calculated by 100 bootstrap resamples. Predictors chosen in ≥50% bootstrapped selection routines will be taken forward.

For the final model, bias-corrected ROC (receiver operating characteristic) curves and calibration plots will be provided. All model coefficients with SEs, and ORs with 95% CIs will be reported.

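### MAPE as defined (prediction against the 0/1 outcome) cannot be 0.048 at the planned AUC of 0.86, and it is an improper score to report in cross-validation

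*Protocol article*

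**What the plan says.** The Sample size section gives MAPE as a planning criterion, "defined as the mean absolute difference between predicted and observed outcomes (cancer=1, no cancer=0". No other definition appears in the article. The section then states: "The resulting CPM based on 615 participants will have an MAPE of 0.048, estimate cancer incidence with precision 0.088". It gives the minimum Cox-Snell R² as a value "of 0.431 based on forty predictors", and for discrimination it says: "The SE in the AUC achieved by the CPM will be 0.016, based on an AUC of 0.86". There are 205 cases and the same number in each of two control groups ("We aim to recruit the same number of each type of control, totalling 615 participants with complete data"), so the case fraction is 205/615 = 1/3.

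The section on developing and reporting the CPM uses the same term for performance. In each fold, "the sensitivity, AUC, precision-recall AUC and the MAPE will be calculated and summarised by median (IQR) values across folds". It also says that the best-performing model is identified by nested cross-validation, without naming the deciding measure, and it plans calibration plots for the final model. The section on diagnostic rules derives thresholds for referral, review and discharge from the final model's probabilities.

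**The concern.** Two things are wrong as written.

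**The figure does not fit the definition.** The distance between a probability and a 0/1 outcome stays large even for a perfect risk model, because a person with a true risk of 0.4 is either a case or not. A value of 0.048 on that scale means near-perfect separation, which an AUC of 0.86 is not. If the cross-validated MAPE comes out near 0.28, it will look like a failure against the promised 0.048 although the model did what was planned.

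**The measure rewards the wrong thing.** Absolute error against a 0/1 outcome is not a proper score, since it is lowest when predictions are pushed to 0 or 1. LASSO, elastic net, random forest and deep neural networks can differ in how extreme their probabilities are. The clinical thresholds are later set on those probabilities, so the fold-level summary should not favour overconfidence. None of the other three fold measures rewards calibration: AUC and precision-recall AUC depend only on ranking, and sensitivity depends on a cut-off.

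**Working it through.** **Inputs (Sample size section).** N = 615; 205 cases; case fraction φ = 1/3; AUC 0.86; Cox-Snell R² 0.431; 40 predictors; MAPE 0.048. Assumed here, not stated in the article: two-sided α of 0.05, a target shrinkage of 0.9, and an equal-variance binormal score where marked.

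**1. The neighbouring figures reproduce, so the inputs are read correctly.**
- Cases: (1.960 + 0.842)² × 0.85 × 0.15 / 0.07² = 204.2, rounded up to 205.
- Recruitment: 205/0.8 = 256.25, rounded up to 257; 3 × 257 = 771.
- R²: 40 / [(0.9 − 1) × ln(1 − 0.431/0.9)] = 613.7, close to 615.
- SE of the AUC: 0.0161 with the Newcombe variant (Hanley-McNeil gives 0.0176), against 0.016 stated.

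**2. The 0.048 does not reproduce under the stated definition.** With y the outcome and p a calibrated prediction, E|y − p| = E[p(1 − p) + (1 − p)p] = 2E[p(1 − p)]. Take a binormal score with equal variances, mean separation √2 × Φ⁻¹(AUC) and φ = 1/3, and integrate:

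| Setting | mean \|y − p\| | relative to 0.048 |
|---|---|---|
| AUC 0.86 | 0.278 | 5.8 times |
| R² 0.431 (AUC about 0.91) | 0.223 | 4.7 times |
| AUC about 0.995 | 0.048 | 1 |

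**3. A floor that does not need the binormal form.** Mean |y − p| cannot be lower than the smallest misclassification error available from the score. That error is φ(1 − sensitivity) + (1 − φ)(1 − specificity). As φ is below one half, this is at least φ(1 − J), where J is the Youden index. For a concave ROC curve, which every calibrated model has, J ≤ 2 × AUC − 1 = 0.72. The floor is (1/3)(1 − 0.72) = 0.093, which is 1.9 times 0.048. Rescaling the predictions monotonically does not escape it.

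Concavity is needed. Without it the bound drops to (1/3)(1 − 0.86) = 0.047. That value arises only in a degenerate case: 86% of cases rank above every control, the other 14% rank below every control, and all predictions are 0 or 1. No realistic model behaves so.

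**4. The measure is improper.** For true risk q and prediction p, the expected loss is q(1 − p) + (1 − q)p = q + p(1 − 2q). This is linear in p, so it is smallest at p = 0 when q < 0.5 and at p = 1 when q > 0.5. It is not smallest at p = q, apart from the tie at q = 0.5. With AUC 0.86, φ = 1/3 and the binormal score, multiply the correct log-odds by k:

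| k | mean \|y − p\| | Brier |
|---|---|---|
| 0.5 (underconfident) | 0.352 | 0.152 |
| 1 (calibrated) | 0.278 | 0.139 |
| 2 | 0.229 | 0.149 |
| 5 | 0.206 | 0.173 |
| 20 | 0.201 | 0.193 |

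The ranking is the same in every row, so AUC and precision-recall AUC do not change. MAPE improves all the way down; the Brier score is best at k = 1.

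**5. After the change.** The Brier score of a calibrated model in this setting is 0.139 and any rescaling makes it worse. If MAPE is redefined as |predicted − true risk|, a perfectly calibrated model under this setup scores 0, so a small planning value is coherent. True risk is not observed, however, so that version cannot be computed in a validation fold.

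**The case against.** A reader might infer that the winning model is chosen on MAPE, and so that an overconfident model will supply the thresholds. The document does not support this. MAPE is one of four fold measures, all of them said only to be calculated and summarised; the measure that decides is not named and may be fixed in an analysis plan not shown here.

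Crude abuses of the measure would also be seen. Predicting 0 for everyone scores 0.333, better than the 0.444 (2 × 1/3 × 2/3) from giving everyone the base rate, but its sensitivity is 0 and its AUC 0.5. Rounding predictions at 0.5 in the binormal setting gives sensitivity 0.62 and specificity 0.89, so the AUC drops to (0.62 + 0.89)/2, about 0.755. What AUC and precision-recall AUC cannot see is order-preserving overconfidence, as in step 4.

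Nor is calibration ignored. Calibration plots are planned for the final model, bootstrap optimism is estimated, and net benefit and decision curves depend on the predicted probabilities. These safeguards are real and limit the harm. But the plots are promised for the final model only, so they do not help when model families are compared.

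Finally, the 0.28 rests on a distributional assumption. That is fair, and it is why the 0.093 floor and the 0.22 at the stated R² are given beside it. All three exceed 0.048.

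**Conclusion.** The point holds. Under the article's own definition, MAPE 0.048 is incompatible with an AUC of 0.86 at a case fraction of 1/3. The shortfall is at least a factor of about two for any model with a concave ROC curve, and about five to six under the equal-variance binormal assumption. The impropriety of the measure follows from algebra; its size in the table uses the binormal assumption.

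The consequence is limited to a misleading comparison of model families in cross-validation and a misreading of results against 0.048. A wrong model selection is not shown. It is also not shown that the 615 participants are too few: the article may have meant another quantity by MAPE, and whether 0.048 is right for that quantity cannot be settled from this document.

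**What to change.** - **Developing and reporting the CPM:** replace MAPE among the fold measures with the Brier score, plus calibration slope and intercept on held-out predictions, for every model family.
- **Sample size:** reconcile the definition with the figure. If MAPE is meant as the mean absolute difference between predicted and true risk, say so, use it for planning only, and recompute and restate 0.048 under that definition with its inputs. Changing the words and keeping the number unchecked is not enough.

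The cost is wording, one recalculation and a different summary of predictions that will exist anyway. No new data or design change is needed for the reporting change; whether a restated planning value has any bearing on sample size will be known only once it is recomputed.

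### The stated MAPE of 0.048 and incidence precision of 0.088 do not follow from 615 participants, a one-third case fraction and forty predictors, and the printed MAPE definition fits neither value

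*Protocol article*

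**What the plan says.** All of this is in the Sample size section of the protocol article unless another section is named.

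- The number of cases comes from sensitivity: "The sample size of 205 PDAC cases was based on a target sensitivity of 85%, with 7% precision and 80% power".
- The controls follow from it: "We aim to recruit the same number of each type of control, totalling 615 participants with complete data". The case fraction is therefore 205/615 = 1/3.
- MAPE is introduced as a further adequacy measure, "defined as the mean absolute difference between predicted and observed outcomes (cancer=1, no cancer=0").
- The claimed performance is: "The resulting CPM based on 615 participants will have an MAPE of 0.048, estimate cancer incidence with precision 0.088". The sentence goes on to say that the model will "achieve a minimum Cox-Snell R^2^ of 0.431 based on forty predictors".
- The discrimination claim is: "The SE in the AUC achieved by the CPM will be 0.016, based on an AUC of 0.86".
- The Study design section describes the design: "VAPOR 1 is a UK prospective case–control study".

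**The concern.** The sentence gives two figures as evidence that 615 participants are enough to develop the model. Both can be recomputed from inputs in the same section, and neither comes out as printed. The figure labelled as precision equals the MAPE for these inputs, and the figure labelled as MAPE is well below it.

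MAPE describes how far individual predicted risks are expected to lie from the truth. The section on diagnostic rules sets thresholds for referral, review and discharge on those predicted risks, and the internal validation plan reports MAPE for each fold. A reader will compare the reported values with 0.048. That benchmark is unsupported for forty predictors, and on the printed definition it cannot be reached.

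**Working it through.** **Inputs from the Sample size section.** n = 615; cases = 205, so φ = 1/3; P = 40 predictors; AUC = 0.86. The confidence level for the precision is not stated, so 95% two-sided is assumed and alternatives are shown.

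**Step 1. Reproduce the neighbouring figures, to confirm the inputs.**
- Cases: (1.96 + 0.84)² × 0.85 × 0.15 / 0.07² = 204.2, so 205.
- Recruitment: 205/0.8 = 256.25, rounded up to 257 per group; 3 × 257 = 771.
- Minimum Cox-Snell R² at shrinkage S = 0.9 (assumed): S × (1 − exp(−P/(n(1 − S)))) = 0.9 × (1 − exp(−40/61.5)) = 0.430. Stated: 0.431.
- SE of the AUC by Newcombe's formula at AUC 0.86, n = 615, φ = 1/3: 0.0161. Stated: 0.016.

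The R² figure needs n = 615 and P = 40 together, so these are the inputs that were used.

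**Step 2. MAPE.** The standard sample-size formula is ln(MAPE) = −0.508 + 0.259 ln φ + 0.504 ln P − 0.544 ln n.
- P = 40: −0.508 − 0.285 + 1.859 − 3.493 = −2.427, so MAPE = 0.0883.
- P = 50 (roughly the number of VOCs kept after screening, per the model development section): 0.0988.

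The coefficients are not in the document, so the result was checked by simulation without the formula: unpenalised logistic regression, n = 615, P = 40, prevalence 1/3. Mean |predicted − true risk| was 0.084 at AUC 0.85 and 0.079 at AUC 0.88. It stayed between 0.079 and 0.100 over AUCs from 0.88 down to 0.63.

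**Step 3. Precision of the case fraction.** The SE is √((1/3)(2/3)/615) = 0.0190.

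| Reading of precision | Value |
|---|---|
| SE | 0.019 |
| 95% half-width, 1.96 × SE | 0.0373 |
| 99% half-width | 0.049 |
| (z for 5% two-sided + z for 80% power) × SE | 0.053 |
| 95% full width | 0.0745 |
| 95% full width if the fraction were 0.5 | 0.079 |
| Stated | 0.088 |

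None gives 0.088. A 95% half-width of 0.088 corresponds to (1.96/0.088)² × 2/9 ≈ 110 participants.

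**Step 4. The printed definition of MAPE.** If predictions are compared with observed 0/1 outcomes, a model that knows each true risk p still has expected error 2p(1 − p), averaged over participants. With normally distributed log-odds and prevalence 1/3, simulation gives 0.292 at AUC 0.85 and 0.260 at AUC 0.88. At AUC 0.86 the value is about 0.28. On that definition neither 0.048 nor 0.088 is possible at the stated AUC.

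**The case against.** **The sample size does not depend on these figures.** This stands. The targets of 205, 615 and 771 come from the sensitivity calculation, and MAPE and precision are reported afterwards as properties of that size. Actual prediction error will be estimated by cross-validation and the bootstrap. This limits the severity but does not make the sentence right.

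**The plan uses LASSO and elastic net, so 0.088 is too pessimistic.** This stands in part. The formula and the simulation above describe an unpenalised fit. A small simulation of cross-validated LASSO (25 replicates, n = 615, 40 candidates, AUC 0.86) gave errors against true risk of 0.057 with 5 true predictors, 0.069 with 10, 0.072 with 20 and 0.085 with all 40. Penalisation can bring the error well below 0.088, but no run reached 0.048, and the section reports no penalised calculation.

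**Forty predictors may attach only to the R².** The section gives no other number of predictors, and the precision figure does not depend on that number at all.

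**Incidence may loosely mean the proportion of cases in the sample.** This is plausible, and the document plans no incidence estimate. The word is still wrong for a fraction set by recruiting equal groups, and 0.088 is not the precision of that fraction either.

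**Stronger readings that the document does not support.** A reader might infer that the two numbers were simply swapped. They were not: 0.088 is the MAPE, but 0.048 is not the 95% half-width for 615 at 1/3, and the 99% half-width is 0.049. Other origins can be guessed at, but the document does not show which applies. A reader might also infer that prediction error is understated by a fixed factor of 0.088/0.048 = 1.8, or that the study is too small. The ratio holds only for the unpenalised formula value, and a misplaced label is as likely as an inflated claim.

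**Conclusion.** Both printed figures are wrong for their labels. For n = 615, φ = 1/3 and P = 40, the MAPE is about 0.088 rather than 0.048, and the 95% half-width of the case fraction is about 0.037 rather than 0.088. The printed definition of MAPE is inconsistent with either value, since it implies about 0.28 even for true risks at AUC 0.86.

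The precision result is plain arithmetic and survives every usual choice of confidence level or width. The MAPE result assumes an unpenalised logistic model and error measured against true risk. The value of about 0.28 assumes normally distributed log-odds. The source of 0.048 is unknown. Recruitment targets, the R² and the SE of the AUC are unaffected. Severity: should-fix.

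**What to change.** In the Sample size section:

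1. Restate the MAPE as about 0.09 for 40 predictors, and about 0.10 for the roughly 50 VOCs kept after screening. Say that this is the formula value for an unpenalised model and that penalised fitting may give a lower value.
2. Define this MAPE as the mean absolute difference between predicted and true risk. If the per-fold MAPE in the internal validation is computed against observed 0/1 outcomes, say there that it is a different quantity, not comparable with the planning value.
3. Restate the precision as ±0.037 (95%) for the proportion of cases in the study sample, and remove the word incidence.

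The cost is a text correction, with a less favourable MAPE on paper. It needs no extra participants and no change to the modelling strategy or the targets of 205, 615 and 771.
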